## Abstract

**Background:**

“Determined, Resilient, AIDS-free, Mentored and Safe” (DREAMS) is a package of biomedical, social and economic interventions offered to adolescent girls and young women aged 10–24 years with the aim of reducing HIV incidence. In four of the six DREAMS districts in Zimbabwe, DREAMS includes an offer of oral pre-exposure prophylaxis (DREAMS+PrEP), alongside interventions to support demand and adherence, to women aged 18–24 who are at highest risk of HIV infection, including young women who sell sex (YWSS). This evaluation study addresses the question: does the delivery of DREAMS+PrEP through various providers reduce HIV incidence among YWSS Zimbabwe? We describe our approach to designing a rigorous study to assess whether DREAMS+PrEP had an impact on HIV incidence.

**Methods:**

The study design needed to account for the fact that: 1) DREAMS+PrEP was non-randomly allocated; 2) there is no sampling frame for the target population for the evaluation; 3) there are a small number of DREAMS districts (*N* = 6), and 4) DREAMS+PrEP is being implemented by various providers. The study will use a cohort analysis approach to compare HIV incidence among YWSS in two DREAMS+PrEP districts to HIV incidence among YWSS in non-DREAMS comparison sites. YWSS will be referred to services and recruited into the cohort through a network-based (respondent-driven) recruitment strategy, and followed-up 12- and 24-months after enrolment. Women will be asked to complete a questionnaire and offered HIV testing. Additional complications of this study include identifying comparable populations of YWSS in the DREAMS+PrEP and non-DREAMS comparison sites, and retention of YWSS over the 24-month period. The primary outcome is HIV incidence among YWSS HIV-negative at study enrolment measured by repeat, rapid HIV testing over 24-months. Inference will be based on plausibility that DREAMS+PrEP had an impact on HIV incidence. A process evaluation will be conducted to understand intervention implementation, and document any contextual factors determining the success or failure of intervention delivery.

**Discussion:**

HIV prevention products of known efficacy are available. Innovative studies are needed to provide evidence of how to optimise product use through combination interventions to achieve population impact within different contexts. We describe the design of such a study.

## Background

In public health, one aim of implementation science studies, including impact evaluations, is to understand whether and how interventions with known efficacy should be delivered to have a population-level impact in real-life settings. Interventions supporting delivery are often complex, taking the form of a package of strategies to support demand for, use and adherence to prevention behaviours and/or technologies. Contextual adaptation for effective delivery may be critical to achieve impact. Randomised allocation may not be feasible in some settings, posing challenges to such studies. Implementation science studies therefore require innovation in study design, and pre-published protocols for these studies are particularly important yet less commonly published than for randomised trials.

In this protocol paper, we describe the evaluation of a complex and ambitious intervention package being delivered by multiple providers with the aim of reducing HIV infection rates among high-risk young women in Zimbabwe. We outline challenges faced in designing a rigorous study to estimate the impact of the intervention in this situation, and describe our proposed design, analysis strategy and approach to inference.

Across sub-Saharan Africa, adolescent girls and young women (AGYW) are at disproportionately higher risk of HIV than older females and their male peers [1, 2]. This increased risk is driven by a combination of biological, behavioural and structural factors [3]. At highest risk of infection are young female sex workers (FSW) and other young women who sell sex (YWSS) for financial or material resources [4]. Relative to older FSW, young FSW and YWSS aged under 25 years are at increased risk due to economic vulnerability, sexual partnerships with older men more likely to than younger men to have prevalent infection, and reduced skills in condom use negotiation [5–8]. Limited access to available health services for fear of stigma and discrimination further increases their risk of HIV and other health outcomes [5, 7]. In Zimbabwe, our experience is that YWSS, those under 25 years as well as those who have most recently begun sex work, may not identify as sex workers. Consequently, they are less likely to access sex work specific services [4, 9]. Younger FSW are also less frequently recruited to research studies of FSW [10, 11]. As such, YWSS are particularly vulnerable to new infection as well as being hidden and complex to conduct evaluation studies with. We anticipate that their risk of new HIV infection is very high; our estimates among young FSW suggest an incidence perhaps as high as 10% per year [9].

In 2015, WHO recommended the use of tenofovir-based oral pre-exposure prophylaxis (PrEP) for individuals at substantial risk of HIV as part of combination HIV prevention [12] based on a systematic review of PrEP studies among a range populations and settings [13]. The review found that PrEP was effective at reducing HIV risk across sexual exposures, PrEP regimen, dosing, and mode of acquisition, and that increased adherence was associated with a demonstrable increase in effectiveness [13]. In trials with adherence > 70%, PrEP reduced risk of infection by 70% (RR = 0.30, 95% CI: 0.21–0.45, *p* = 0.001) [13]. While there is no doubt that, when taken, PrEP is biologically effective in women, pharmacokinetic studies have indicated lower concentrations of tenofovir in vaginal than rectal tissues [14–16] suggesting that adherence is particularly important in women. Evidence from treatment scale-up suggests that younger people find it more difficult to adhere to treatment than older individuals [17], and may require increased adherence support tailored to their age group and lifestyle. In settings where PrEP is available, implementation research is needed to translate the efficacy of PrEP into population-level impact through increased demand and adherence among those at highest risk of HIV, including YWSS. To achieve population-level impact, combined strategies that deliver services that are acceptable and accessible to YWSS, generate demand for, and support use of and adherence to PrEP should be considered [8, 18].

The DREAMS (“Determined, Resilient, Empowered, AIDS-free Mentored, and Safe”) initiative is a package of HIV prevention interventions that aim to synergistically address social, economic, behavioural and biological risk factors that place young women at heightened risk of infection [19, 20]. DREAMS is being implemented in ten sub-Saharan African countries with DREAMS aiming to reduce HIV incidence by 40% among AGYW aged 15–24 years [20]. The package includes social protection (interventions to support young women to remain or return to school, or acquire vocational skills), clinical and prevention services for gender-based violence (GBV), and HIV prevention (HIV testing, STI screening and treatment, condoms). Various providers are implementing these combined interventions in real-world conditions, targeting the most vulnerable, high-risk AGYW. In some settings, including Zimbabwe, PrEP is a component of the package offered to AGYW aged 18 to 24 years at highest risk of HIV (DREAMS+PrEP). This paper outlines the design of a non-randomised, study to estimate the impact of DREAMS+PrEP on HIV incidence among YWSS in two sites in Zimbabwe and to compare this to incidence in sites where DREAMS is not available.

### The DREAMS+PrEP initiative in Zimbabwe

In Zimbabwe, DREAMS is being delivered in six districts by seven implementing partners (IP). IP identify young women who are eligible and likely to benefit from DREAMS, determine their needs and refer them to other IP as appropriate. The route into DREAMS varies according to the specific focus of the IP, for example, entry into DREAMS may be through schools, clinics, HIV testing services or the community more generally. Through this referral process, DREAMS interventions can be “layered” dependent on need. DREAMS targets all vulnerable AGYW aged 10–24 years. In four of the six DREAMS districts, PrEP is being offered to women at highest risk of infection aged 18–24 years, particularly YWSS. PrEP is delivered by PSI Zimbabwe. YWSS are identified through community outreach and mobilisation led by The Centre for Sexual Health and HIV/AIDS Research (CeSHHAR). Community mapping guided the community outreach to identify hotspots where sex is exchanged for material resources. Importantly mapping was not limited to sex work venues.

### Network-based recruitment for referral to services and cohort recruitment

We hypothesise that YWSS exist in sizeable numbers in the DREAMS sites and that they are inter-connected through social networks. To identify these young women, refer them to DREAMS+PrEP services, and recruit them into the impact evaluation study, we will use a network-based recruitment (RDS) strategy that uses social networks to identify and recruit eligible women. At the time of the design of this study, the DREAMS programme selected the 18–24 age cut-off for PrEP. The DREAMS target was to initiate 1400 women aged 18–24 on PrEP, of which 80% would be referred from two DREAMS+PrEP sites. In the two DREAMS+PrEP sites, PSI will deliver PrEP. To support uptake and adherence to PrEP, community mobilisation activities, PrEP adherence support groups and peer outreach services will be specifically targeted to YWSS. *Sisters with a Voice* (*Sisters*) programme, an existing national FSW programme that offers HIV care and prevention services, will deliver these services. Initiated in 2009, *Sisters* provides HIV targeted services to FSW in 36 sites across Zimbabwe in line with WHO guidance [4, 9]. The *Young Sisters* programme offers services specifically tailored for younger women aged 15–19 years [4].

The community mapping allowed for the identification and recruitment of “seeds” to start the network-based recruitment process (Fig. 1). A “seed” is a participant purposively selected to start recruitment. Seeds will be drawn from different ages (between 18 and 24 years), types of selling sex/exchanging sex for resources and geographical spread across each site as identified in community mapping. Each seed will be offered two coupons and asked to recruit two young women who they think meets the inclusion criteria [21], namely: the recruit should be a young woman aged 18–24 whom they know (defined as seeing each other at least once a month) who also exchanges sex with men for money and/or resources. Our definition of “selling sex” includes young women who self-identify as FSW and extends to young women who have sex with men in exchange for money and/or resources and report the sex would not occur in the absence of this exchange (but do not think of themselves as sex workers). Women receiving a coupon who attend the study site for enrolment (“recruits”) will also be given two coupons to recruit two peers. In all impact evaluation sites, six iterations of this process (“waves”) will be completed to refer YWSS to services and recruit the sample size required for the impact evaluation as described below.

**Fig. 1 Fig1:**
[figure not shown]
Schematic of the processes involved in this study to identify, reach and refer young women who sell sex to services and recruit these same women into an impact evaluation cohort

Once reached, women attending the study site will be referred to DREAMS+PrEP interventions dependent on need and recruited to the impact evaluation. The same strategy is being implemented in four non-DREAMS comparison sites, with YWSS referred to the *Sisters* programme and/or other appropriate services available in these sites. Services offered at *Sisters* clinics include: STI screening and treatment, HIV testing with referrals to government services for treatment, free condoms and contraception, and legal advice supported by a network of peer educators.

### Key considerations for study design

We seek to estimate the impact of the DREAMS+PrEP intervention on HIV incidence among YWSS aged 18–24. The DREAMS+PrEP intervention includes identifying high risk women, referral for an offer of PrEP for those testing negative, and referral to other DREAMS interventions, depending on need and availability, that will support use and adherence through a variety of behavioural and structural interventions. This impact evaluation has four main design challenges. First, it was not possible to randomise study sites to receive the DREAMS intervention. DREAMS districts were selected through country-level consultation and based on population of AGYW and HIV burden. Second, YWSS, the target group for this evaluation are a “hidden” population for which a sampling frame does not exist. Third, there are few intervention districts, and 80% of the intended beneficiaries that fall within our target group will be recruited from only two districts. Fourth, there are numerous providers and the strategies to identify, reach and refer YWSS to services is complex.

Our overall approach to these design challenges is to: 1) use existing data (from the *Sisters* programme) to select comparison sites comparable to the DREAMS+PrEP sites in factors known to influence HIV risk; 2) leverage the use of the network-based (respondent driven) strategy that is being used to identify and reach YWSS, refer these YWSS to services, in order to recruit them into the impact evaluation, and repeat this process in the non-DREAMS comparison sites; 3) take a cohort analysis approach to compare HIV incidence among YWSS in the DREAMS+PrEP sites with YWSS in the non-DREAMS comparison sites, and collect data on recent infection and risk factors for HIV incidence at enrolment in support of an adjusted analysis; 4) embed a process evaluation within the impact evaluation to seek to understand intervention implementation, and document any contextual factors determining the success or failure of delivery of intervention components.

## Methods

### Study location and non-randomised site selection

We will conduct this study in two DREAMS+PrEP and four non-DREAMS comparison sites. We selected the two DREAMS+PrEP sites, as these sites will refer the largest proportion of young women to PrEP and supportive interventions. These two sites are cities, among the largest in Zimbabwe, with a combined population of over 500,000. Each site has a static *Sisters* programme clinic that offers walk-in clinical services Monday to Friday each week [9].

We selected comparison sites from the 36 sites where the *Sisters* programme is operational [9]. Of the 36 national *Sisters* sites, six are static sites in larger towns and cities that provide walk-in services on weekdays and 30 are mobile sites in smaller towns where outreach services are delivered weekly. From the *Sisters* sites, we first excluded sites that overlapped with DREAMS, excluded seven sites where an HIV treatment and prevention, including PrEP, intervention trial (SAPPH-Ire trial) had been implemented [17], and a site where another organisation is delivering PrEP. Second, we excluded 15 rural sites. From the remaining eight urban sites, we selected four comparison sites using routine *Sisters* programme data and expert opinion. We selected one site as it is a large town with a static *Sisters* clinic where > 1500 FSW were registered by mid-2016, of whom 25% were aged 18 to 24. Of the remaining seven sites we selected three sites because they each had: 1) > 400 FSW registered with the programme; 2) among whom > 20% were aged 18–24, and 3) each site was a similar distance to Harare as the two DREAMS+PrEP sites.

### Measurements and sample collection

Young women recruited to the impact evaluation study will be asked to provide written consent to complete a questionnaire, provide a dried blood spot (DBS) and have a rapid HIV test. Women will be followed-up at 12 and 24 months, and asked to complete an interviewer-administered questionnaire and offered HIV testing services using a rapid HIV test-kit. The questionnaire will cover socio-demographic factors, a range of behavioural characteristics, access to health and/or social-support services, and HIV-related questions. We will use the DBS collected at enrolment to test for HIV, and, for those who test HIV-positive, to determine prevalence of recent infection using Recent Infection Testing Algorithm (RITA), which includes use of the LAG avidity assay coupled with viral load testing.

### Retention and follow-up procedures

To assist with retention of the cohort, women will be asked to provide their phone number and residential information, and informed that the information will be used to send follow-up reminders via WhatsApp® or through home visits 12- and 24-months after enrolment. We will exclude young women who report that they are planning to move away from the district within the next six months. Locator information will be checked for completeness and accuracy at each visit. To support retention in the programme, curated WhatsApp® broadcast groups of approximately 50 participants each will be developed. The curator will send messages but the broadcasts will not disclose who is in the group or share any phone numbers.

### Primary outcome measurement

The primary outcome is HIV incidence over the 24 months following enrolment into the study, the numerator will be the number of new infections among young women testing HIV-negative at enrolment, the denominator the person-years of follow-up. Person-years of follow-up for each YWSS will be calculated as: 1) time between the first HIV negative test at enrolment and an HIV negative test at 12 months and 24 months; or 2) the mid-point between an HIV negative test and an HIV positive test. If a participant is lost to follow-up (LTFU), the participant will be censored at last HIV-negative test.

### Secondary outcomes

This study has many secondary outcomes, including reduced food insecurity, reduced condom-less sex with sexual partners, reduced experience of violence from partners and police, reduced reliance on sex work for economic reasons, increased uptake of HIV testing services and access to STI treatment services, and self-reported adherence to ART or PrEP.

### Ethical approval

We received ethical approval for this study from the Medical Research Council of Zimbabwe (Reference number MRCZ/A/2085) and the London School of Hygiene and Tropical Medicine (Reference number 11835).

### Statistical analysis

We aim to adhere to the transparent reporting principles of TREND [22]. In addition, we will report on items essential to the network-based (RDS) recruitment as per the STROBE-RDS extension [23]. We will finalise a statistical analysis plan before data collection at 24-months is complete.

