### Assessing balance across sites

Using enrolment data, we will describe characteristics of the YWSS recruited into the DREAMS+PrEP and non-DREAMS comparison cohorts. To assess whether there is any imbalance across the two cohorts in risk factors for HIV, we will conduct a comparative analysis of the socio-demographic characteristics, sexual behaviours of the YWSS recruited to the impact evaluation, and prevalent and recent infection. Where there is evidence of imbalance in factors likely to influence HIV risk, we will adjust for these individual-level factors in our analysis of the primary outcome as described below.

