### Stages of primary outcome analysis

We will adopt a transparent and simple cohort approach to the analysis of the primary outcome. Our approach to inference will consider whether it is plausible that DREAMS+PrEP had an impact on HIV incidence among the target population [28, 29].

We will conduct our primary analysis in three phases. Each stage aims to build the strength of the evidence base of a plausible causal impact of DREAMS on HIV incidence. In phase one, we will take an individual-level cohort analysis approach. At 24-months, we will describe the number of women retained in the cohort and summarise follow-up time (average and total) in the DREAMS+PrEP and comparison sites. We will describe HIV incidence at 24 months in the DREAMS+PrEP and comparison groups with associated 95%CI. We will also describe site-specific estimates of incidence. Using Poisson regression, we will compare the incidence rates at 24-months across the two groups expressed as an unadjusted rate ratio with associated 95%CI presented. To account for the RDS design, we will weight the data by 1/self-reported degree of social network.

The unadjusted rate ratio is subject to confounding by risk factors for HIV that are differential across the two groups in the absence of random allocation and the small number of sites. In phase two, we will estimate a rate ratio adjusted for potential confounders. We will present the adjusted rate ratio with associated 95%CI.

In the third phase, we will assess whether there is evidence for an association between individual-level exposure to DREAMS+PrEP interventions and HIV incidence. For example, we will compare the risk of HIV infection between women self-reporting that they are adherent to PrEP and women who did not take PrEP. We will specify the exact measures of exposure after the year 1 data have been collected, without reference to the outcome data and before the final follow-up.

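### The analysis plan may be finalised after most infections are recorded, with no outcome-blind condition, and the article does not say whether the unadjusted or the adjusted rate ratio is primary

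*Protocol article*

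**What the plan says.** In the Protocol article, the section Statistical analysis gives one timing rule for the plan as a whole: "We will finalise a statistical analysis plan before data collection at 24-months is complete".

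The section Stages of primary outcome analysis then states: "We will conduct our primary analysis in three phases".

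- **Phase 1** is specified: "Using Poisson regression, we will compare the incidence rates at 24-months across the two groups expressed as an unadjusted rate ratio", with a 95% CI, and "we will weight the data by 1/self-reported degree of social network". The same section then says that this ratio is open to confounding.
- **Phase 2** is stated in outline: "In phase two, we will estimate a rate ratio adjusted for potential confounders", again with a 95% CI. The section Assessing balance across sites says where the confounders come from: "Where there is evidence of imbalance in factors likely to influence HIV risk, we will adjust for these individual-level factors". That comparison uses enrolment data. No list of factors and no threshold for imbalance is given.
- **Phase 3** relates individual exposure to HIV incidence. Its exposure measures are to be fixed once year 1 data are in, "without reference to the outcome data and before the final follow-up".

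The section Sample size justification powers a two-group comparison of incidence: 80% power for a reduction of 40% or more at p = 0.05, with 1200 women per group.

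**The concern.** Leaving detail to an analysis plan is sound practice if the plan is fixed before outcomes can inform it. The deadline here does not secure that. It falls after the 12-month HIV results and after most of the 24-month results have been collected. Because intervention and comparison groups are different sites, anyone who holds results by site holds them by group.

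The authors saw the risk for phase 3 and guarded against it there. The group comparison, on which the study is powered, has no such guard. In a non-randomised study with two intervention and four comparison sites, the choice of confounders may move the adjusted ratio appreciably. Readers need to know that this choice was made without sight of the result.

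The second issue is the label. If the unadjusted and adjusted ratios disagree, the article does not say which one answers the 40% question.

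**Working it through.** **1. Which comparison does the stated power describe?** Table 1 can be reproduced with a Wald test on the log of two rates, assuming two-sided alpha 0.05 (sidedness is not stated):

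power = Φ( |ln RR| / √(1/e₀ + 1/e₁) − 1.96 ), where e = rate × person-years.

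For comparison incidence 5.0 per 100 person-years, 1500 person-years per cohort and a 40% reduction:
- e₀ = 0.05 × 1500 = 75 and e₁ = 0.03 × 1500 = 45
- √(1/75 + 1/45) = 0.1886 and |ln 0.60| = 0.5108
- 0.5108/0.1886 − 1.96 = 0.75, so power is 77.3% (Table 1: 77)

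| Incidence per 100 person-years | 1500 person-years: Table 1 / recomputed | 1380 person-years: Table 1 / recomputed |
|---|---|---|
| 5.0 | 77 / 77.3 | 75 / 73.8 |
| 6.0 | 85 / 84.3 | 82 / 81.2 |
| 7.0 | 90 / 89.4 | 87 / 86.7 |
| 8.0 | 93 / 92.9 | 91 / 90.8 |

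All 24 cells of Table 1 agree within 2 points. The power arithmetic is that of an unadjusted two-group rate comparison. It therefore excludes phase 3, and its form is that of phase 1, the ratio the article itself calls confounded.

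**2. How much outcome information can exist before the plan is final?**

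Inputs from the article: 1200 women per cohort, 20% HIV-positive at enrolment (1200 × 0.8 = 960 at risk), 30% lost over 24 months, comparison incidence 5.0–8.0 per 100 person-years.

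Assumptions: constant incidence λ, taken from 0.03 (a 40% reduction from 0.05) to 0.08 per year; a proportion L lost by month 12, which the article does not give, ranged from 0 to 30%.

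- Infections found at 12 months: 960 × (1 − L) × (1 − e^−λ)
- Infections found at 24 months: 960 × 0.7 × e^−λ × (1 − e^−λ)

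With λ = 0.05 and L = 0.15 these are 39.8 and 31.2 per cohort. The share recorded after the 12-month round is 39.8/(39.8 + 31.2) = 56%. Over the full range it runs from 51% (λ = 0.03, L = 0.30) to 61% (λ = 0.08, L = 0).

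Continuing with λ = 0.05 and L = 0.15, the share is (39.8 + f × 31.2)/71.0 when a fraction f of the 24-month visits is done:

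| 24-month visits done | Infections recorded |
|---|---|
| 0% | 56% |
| 50% | 78% |
| 90% | 96% |
| 95% | 98% |

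Every row is a date that the stated deadline allows.

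**3. What is still open at that date?**

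| Element | Fixed in the article? | Covered by the outcome-blind rule? |
|---|---|---|
| Outcome, person-time, censoring | Yes | Not needed |
| Phase 1 model and weight | Yes | Not needed |
| Phase 2 confounder set and imbalance criterion | Source only (enrolment data) | No |
| Remaining phase 2 specification, including whether the phase 1 weight is kept | No | No |
| Phase 3 exposure measures | Deferred until year 1 data are in | Yes |
| Which ratio answers the 40% question | No | No |

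**The case against.** The strongest reply is that much is already settled. The outcome definition, the phase 1 model and the weight are in the article. Adjustment is tied to enrolment imbalance, not to outcomes. An exact covariate list is something a protocol commonly leaves to the analysis plan. All of this stands, and the absence of a list is not the complaint. The complaint is the deadline, which the article does state and which a later document cannot repair if it is itself written late.

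A reader might infer that any favourable phase could become the conclusion, and calculate an inflated false-positive rate from two or three chances at p = 0.05. The article does not support this. The phases are ordered and cumulative ("Each stage aims to build the strength of the evidence base of a plausible causal impact of DREAMS on HIV incidence"), both ratios are to be presented, phase 3 is not the powered comparison, and no rule declares success from any one phase. Phases 1 and 2 also use the same women and infections, so treating them as independent tests would be wrong.

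A reader might also take the two timing rules as contradictory. They are compatible: the phase 3 rule is an added safeguard. Nor does the article say that anyone will tabulate outcomes by group early. Blinding is not mentioned, and collected results are not the same as results seen. What remains is that nothing in the text rules this out.

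Finally, the text leans towards the adjusted ratio by calling the unadjusted one confounded and promising adjustment where there is imbalance. That is fair, but it is an inference the article could replace with one sentence.

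**Conclusion.** The point holds in a limited form. The deadline permits the plan to be finalised when more than half, and possibly nearly all, of the infections have been recorded, with no requirement that results by group or site be unseen. The unprotected choices are the phase 2 confounder set, the imbalance criterion and the rest of the phase 2 specification. Separately, the powered two-group question has two candidate answers and neither is named as primary.

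The shares of infections rest on constant incidence, the article's own figures for prevalence and loss, and an assumed loss by month 12. The lower bound stays just above one half across the range tried. The resulting bias cannot be sized from the article, because it depends on who sees what and when. This is an inexpensive improvement to credibility, not evidence that the analysis will be chosen to suit the result.

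**What to change.** 1. In Statistical analysis, replace the deadline with a commitment that the whole plan is finalised without reference to follow-up outcome data, and before any follow-up HIV result is tabulated by group or site. This extends to the full plan the rule already adopted for phase 3. Enrolment HIV and recent-infection results stay available, since the balance assessment needs them.
2. In Stages of primary outcome analysis, name the phase 2 adjusted rate ratio as the primary estimate for the 40% reduction at p = 0.05. Report phase 1 alongside it as descriptive, and phase 3 as supportive.
3. Put the confounder set, or the imbalance criterion that selects it, and the phase 2 weighting into the plan under that same rule.

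The cost is a few sentences and an analysis plan completed some months earlier. No change to recruitment, data collection or sample size is needed.
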